### Machine learning

The machine learning models in this study will be trained to perform the following tasks: (1) to predict whether a subject has or does not have psychiatric disorders such as depression, bipolar disorder, anxiety disorder, schizophrenia, or dementia; (2) to predict the severity of a subject's state based on the results of rating scales such as the Hamilton Rating Scale for Depression (HAM-D), the Young Mania Rating Scale (YMRS) for bipolar disorder, the Positive And Negative Syndrome Scale (PANSS) for schizophrenia, and MMSE for dementia; (3) to predict the improvement or deterioration of a subject's disorder with respect to a previously recorded state if the subject has undergone a prior assessment; and 4) to predict the scores of individual items in clinical rating scales that are indicators of different aspects of a subject's disorder, such as positive symptoms, negative symptoms, and disorganized symptoms for schizophrenia. The data used to train these machine learning models may include voice features extracted from voice data obtained from subjects, conversational and linguistic information from transcribed text data, and annotations assigned to the data described above.

Next, we will need to perform feature engineering and design the architecture of machine learning. The data, represented through NLP techniques, together with the features obtained through feature engineering processes, will be then used to extract disease features. In particular, disease features extraction will be performed relying on machine learning models such as decision trees, support vector machines (SVM), and deep learning architectures. Each model will be evaluated using cross-validation and then the relative importance of each feature will be estimated using a feature importance estimation method such as XGBoost. We will then evaluate the results using the mean absolute error, coefficient of determination, and correlation coefficients. We also plan to verify whether the features obtained in this manner can distinguish firstly between a normal and disease state, secondly among different diseases, and whether they can distinguish changes in disease severity over time.

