#### Participants

This study is a multicenter, prospective, observational study. Subject recruitment was started in 2018 and is ongoing. Participants are being recruited at seven hospitals and three outpatient clinics in Japan. Patient recruitment is being conducted at the following locations and hospitals: Tokyo (Keio University Hospital, Tsurugaoka Garden Hospital, Oizumi Hospital, Komagino Hospital, Oizumi Mental Clinic, Asakadai Mental Clinic), Kanagawa (Nagatsuta Ikoinomori Clinic), Shiga (Biwako Hospital), Yamagata (Sato Hospital), and Fukushima (Asaka Hospital). Participants are inpatients or outpatients aged ≥20 years who meet the diagnostic criteria for depression, bipolar disorder, schizophrenia, anxiety disorder (including obsessive-compulsive disorder), mild cognitive impairment, or dementia according to the DSM-5 or ICD-11. Healthy volunteers will consist of healthy individuals with no history of psychiatric disorders who have volunteered to participate in the study after reading the research group's website and printed recruitment advertisements and who are at least 20 years old at the time of consent. Researchers will obtain written informed consent about participation in this study and data storage from all the participants. In cases where the patients are judged to be decisionally impaired, the patients' guardians will be asked to provide consent. Participants will be able to leave the study at any time. This study was approved by the Institutional Review Board of Keio University School of Medicine and the participating medical facilities.

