### Sample size

The results of a pilot study conducted on 30 participants prior to the main study showed that the combined NLP and machine learning had an accuracy of 72–80% for binary classification to differentiate between disease and healthy controls (based on a leave-one-out cross-validation). The demographic data in the pilot study are as follows. Age (years, mean ± SD): 56.8 ± 16.9, Gender (%male): 46.7, Diagnosis: 5 schizophrenia, 1 bipolar disorder, 4 depression, 5 anxiety disorder, 5 neurocognitive disorder, and 10 healthy controls.

Specifically, we used the part of speech information as well as feature vectors extracted from the data points using an NLP package called SpaCy as the input to train an XGBoost model for predicting the labels of the data points. We cross-validated the XGBoost model using leave-one-out cross-validation (LOOCV) where we would leave one data point as the test data and train an XGBoost model using the remaining data points. The process repeated for each data point and computed the accuracy of the LOOCV as the ratio of correctly predicted data points out of all of the data points. We further optimized the hyperparameters of the XGBoost model by choosing the set of parameters that has the highest LOOCV accuracy.

We constructed a learning curve to estimate the number of samples required to achieve a classification accuracy of 90%. Starting from a sample size of 15, we randomly sample 15 data points from the total of 30 data points and perform the LOOCV as described above, and repeat the random sampling of 15 data points 10 times, each time keeping track the optimal classification accuracy to get an idea of the distribution of the accuracy for 15 data points.

We then repeat the whole process at one-sample increments until we reach 29 samples. The resulting accuracies are then fitted to a linear model. Based on the parameters of the fitted linear model, we estimated the number of data points required to achieve an accuracy of 90%.

We calculated that a minimum of 50 samples would be required. In addition, considering the variability of the data over a wide range of age groups, severity of illness, and regional differences, it was estimated that about 10 times the number of samples would be necessary. Another means of approximating sample sizes for regression analysis is that the number of cases should be approximately 10 times the number of the independent variables used to obtain statistical confidence (48).

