The challenges of this research are as follows: the difficulty of keeping inter-rater reliability high, the scarcity of previous or similar studies, findings, and datasets in the Japanese-speaking region, and the peculiarity of the Japanese language. First, it will be essential to ensure a similar annotation protocol among the examiners. Similarly, it will be very important to keep the inter-rater reliability high when diagnosing and/or assessing patients. Anticipating this issue, the study team has developed educational modules to maintain a high quality of ratings, and the inter-rater reliability will be tested using random sampling during the study period. Second, as far as we know, this is the first study of this kind to be conducted on such a large sample size in a Japanese-speaking region. The quantity of publicly available conversational data in the Japanese language is relatively small, and almost none is from speakers with mental disorders. To date, most of the reported cases of NLP applied to psychiatric disorders have been conducted in English-speaking areas; therefore, it might be difficult to replicate the findings of the previous studies directly in this study. Finally, we discuss the linguistic characteristics of the Japanese language. Some features cannot exist in Japanese due to differences in grammar. For example, the determiners used to analyze linguistic features of psychosis (37) do not exist in Japanese. Secondly, the Japanese language is agglutinative in that it does not use spaces between words, so its word boundaries are not as clear as they are in other languages. Another challenge involves handling spoken conversational data, which tends to be broken or ill-formed. Furthermore, the Japanese language has the characteristic of often omitting arguments such as subjects. At the same time, however, if common features capable of identifying specific psychiatric disorders across languages can be found, such information would likely become an important disease feature. Although there are many challenges, this research will enable us to study the languages of psychiatric disorders statistically and comprehensively, and it will provide a new interpretation of language to psychiatrists.

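### Cross-validation is the only evaluation named for models built on ten sites, so performance at a site outside the data is not estimated, and some of the reported performance for tasks 1, 2 and 4 may be site or rater recognition

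*Protocol article*

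**What the plan says.** **Evaluation.** The Machine learning section sets four tasks: (1) presence of a disorder, (2) severity score, (3) improvement or deterioration since the person's previous record, and (4) individual scale items. Its evaluation sentence is "Each model will be evaluated using cross-validation", with mean absolute error, R² and correlation as measures. The fold unit is not given. The only cross-validation described in detail is the pilot's, under Sample size: "we would leave one data point as the test data and train an XGBoost model using the remaining data points".

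**Sites.** Under Participants: "Participants are being recruited at seven hospitals and three outpatient clinics in Japan". They are listed under five prefectures, six of the ten under Tokyo, and take both inpatients and outpatients. Healthy controls are people who "volunteered to participate in the study after reading the research group's website and printed recruitment advertisements"; where they are recorded is not said.

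**Recording and features.** Conversation data specifies one headset model, a quiet room (not one common room), a fixed picture order and neutral interviewer wording. Free conversation is left largely unstructured. Data processing and annotation lists formants, cepstral features, n-grams and word embeddings.

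**Variation acknowledged.** Sample size multiplies its minimum by about ten, "considering the variability of the data over a wide range of age groups, severity of illness, and regional differences". The Discussion says "it will be very important to keep the inter-rater reliability high when diagnosing and/or assessing patients", and adds rater training modules and reliability testing on random samples.

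**The concern.** The Abstract's aim is a biomarker that is objective and easy to use, which implies use at clinics that supplied no training data. When every test record comes from a site that is also in the training folds, cross-validation answers a narrower question: how well the model does at these ten sites.

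There is also a possible bias. Suppose one site sees mostly severe patients, or its raters score high, and its recordings are recognisable from room acoustics, regional wording or interviewing style. A model can then gain accuracy or correlation by recognising the site and returning its usual label or score. Keeping a participant's records together does not prevent this, because other participants from that site remain in training. Nor does a larger sample from the same sites. The feature ranking comes from the same modelling step ("Each model will be evaluated using cross-validation and then the relative importance of each feature will be estimated"), so features that mark a site could be listed as disease features.

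**Working it through.** **1. The article's own figures.** Sites: 7 + 3 = 10, and 6 + 1 + 1 + 1 + 1 = 10 are named. Records: 300 × 2 = 600 and 500 × 5 = 2,500, as stated. Desired sample: 10 × 100 variables = 1,000, as stated; the learning-curve route gives 10 × 50 = 500. None of these is in dispute. Neither sample-size route has a term for the number of sites.

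**2. What site identity alone could earn in task 1.** A rule that knows only the site and predicts its majority class has accuracy equal to the mean over sites of max(p, 1 − p), where p is the site's case share. With ten equally spaced shares:
- p = 50% everywhere: 0.50
- p from 30% to 70%: 0.5 + 0.2 × (1 + 7/9 + 5/9 + 3/9 + 1/9)/5 = 0.61
- p from 10% to 90%: 0.5 + 0.4 × (1 + 7/9 + 5/9 + 3/9 + 1/9)/5 = 0.72

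**3. How much of that a model picks up.** The simulation used 10 sites × 40 participants with one record each, 100 features, a ridge classifier (penalty 20, cut-off 0.5) and 100 repetitions. The case shares and the site share of feature variance are assumptions. With one record per person, random 10-fold is already participant-level.

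| Disease signal | Case share by site | Site share of feature variance | Shared-site CV: accuracy / AUC | Leave-one-site-out: accuracy / within-site AUC |
|---|---|---|---|---|
| none | 50% | 20% | 0.498 / 0.492 | 0.499 / 0.495 |
| none | 30–70% | 2% | 0.503 / 0.503 | 0.494 / 0.499 |
| none | 30–70% | 20% | 0.532 / 0.539 | 0.491 / 0.496 |
| none | 10–90% | 2% | 0.528 / 0.538 | 0.483 / 0.501 |
| none | 10–90% | 20% | 0.610 / 0.648 | 0.471 / 0.492 |
| 0.4 SD in 5 features | 50% | 20% | 0.611 / 0.653 | 0.604 / 0.663 |
| 0.4 SD in 5 features | 30–70% | 20% | 0.634 / 0.682 | 0.602 / 0.662 |
| 0.4 SD in 5 features | 10–90% | 20% | 0.686 / 0.750 | 0.575 / 0.647 |

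Without signal, the largest excess over chance is 0.532 − 0.50 ≈ 0.03 at 30–70% and 0.610 − 0.50 = 0.11 at 10–90%. The last three rows have the same disease signal. Shared-site accuracy nevertheless rises by 0.686 − 0.611 = 0.075 as case mix becomes more uneven, while the within-site AUC at held-out sites stays near 0.65.

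**4. Severity scores (tasks 2 and 4).** These runs used ridge regression, 100 patients × 2 records, 10 sites and 100 features, 20 of them with a site signature. The results depend on what is assumed:
- Signature at 30% of those features' variance, no true signal, site explaining 20/30/40% of the scale variance: participant-level r = 0.06/0.10/0.15; leave-one-site-out below 0. With a true signal: 0.57/0.53/0.47 against 0.47/0.40/0.26.
- Weak signature (10%): without signal, r is at most 0.04; with signal at a 40% site share, 0.40 against 0.28.
- Sites differ only by rater offset, which speech cannot show: 0.65 against 0.54 at a 20% share and 0.59 against 0.35 at 40%. At 40% the leave-one-site-out r is 0.53 within sites but 0.35 pooled, so part of the fall comes from pooling.
- Sites differ in true severity and the features track it: 0.72 against 0.69, and 0.73 against 0.66.

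**5. Change since the previous record (task 3).** A constant site or rater offset cancels in a difference between two records of one person. In the same layout with no signal, change-score r was −0.03 at every site share from 0 to 40%.

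**The case against.** **Fold construction is a detail that an article may leave to a fuller document.** This stands as far as it goes. A reader might infer that the folds are random or by record; the article does not say so. The pilot does not settle it, since its 30 data points came from 30 participants. What remains is that cross-validation is the only evaluation named, and that regional differences, which the article itself raises, are met only with more samples.

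**Site differences are not documented.** A reader might infer that each site has its own staff, dialect and case mix. The article gives no staffing, diagnosis or severity by site and does not mention dialect. What it does support is ten sites in five prefectures, a mix of hospitals and clinics, differing rooms, unstructured conversation and a separate recruitment route for controls.

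**Safeguards exist.** One headset model, quiet rooms, fixed pictures, neutral wording, rater training and reliability testing all reduce site effects. None tests performance at a new site. The planned check of linguistic features against diagnostic groups would not screen out a feature that differs between groups because the sites differ.

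**Change over time is also to be verified.** This stands: a fixed site signature cannot track change within a person, so the concern should not be extended to task 3 on these grounds.

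**Conclusion.** The point holds in a limited form. If folds share sites, the reported performance applies to the sampled sites, and nothing in the article estimates performance elsewhere. That conclusion needs no assumption about size.

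The bias is conditional. For tasks 1, 2 and 4, site or rater recognition contributes only if diagnosis mix or mean severity differs by site and the features carry site information. Under the assumptions shown, the excess in task 1 accuracy runs from none to about 0.11. For severity, the gap between participant-level and held-out-site r runs from 0.72 − 0.69 = 0.03 to 0.59 − 0.35 = 0.24, part of the latter being a pooling effect. The article gives no by-site figures to place the study in this range. A reader might conclude that the models will in fact be recognising sites, or that all four tasks are affected; the documents support neither.

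**What to change.** In the Machine learning section:

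- Keep all records of a participant in one fold.
- Add a leave-one-site-out evaluation for tasks 1, 2 and 4, with task 3 optional. Hold out all records of a site together, and merge small clinics into one fold by a rule set before results are seen.
- Report it beside participant-level cross-validation, giving correlation within sites as well as pooled, and base any statement about use at new sites on it. Where a site lacks a class, pool the held-out predictions for task 1.
- Tabulate diagnosis and severity by site, including where healthy controls were recorded. Where controls or a diagnosis come from only one or two sites, state that disease and site cannot be fully separated; leave-one-site-out does not solve that case.

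The cost is an extra run of the same models with different folds. No new data are needed, provided the recording site is on file for each record. The figures may be lower and will be less stable, since there are at most ten held-out units.

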**Aim:**

The purposes of this study are to create a large dataset of Japanese speech data labeled with detailed information on psychiatric disorders and neurocognitive disorders to quantify the linguistic features of those disorders using natural language processing and, finally, to develop objective and easy-to-use biomarkers for diagnosing and assessing the severity of them.

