#### Data processing and annotation

The acquired voice data will be converted into text information using speech recognition technology developed by the research group and will be compensated manually; annotations, such as pauses, fillers, nods, interjections, repetitions, co-supplementation, lexical responses, incomplete sentences, misstatements, etc., will also be made. We will mask the part of personal identifiers such as names when converting voice data into text information. At the same time, the following phonic information will be extracted from the recorded audio data to utilize the physical properties of the audio data in the machine learning model: fundamental frequency (F0); first, second, and third formant frequencies (F1, F2, F3); cepstral peak prominence (CPP); and Mel-frequency cepstrum coefficients (MFCC). These are the major features in speech-language analysis (40). Software such as Praat (41) and openSMILE (42) will be used to extract such phonic information.

Based on the annotated text data thus obtained, various variables are calculated using NLP techniques, such as morphological and syntactic analyses using MeCab (43, 44) and JUMAN (45, 46). For instance, these analyses will include the frequency of the occurrence of each part of speech, vocabulary (negative and positive words), syntactic complexity, length of the utterance, frequency of occurrence of person, use of pronouns and distance to the referent, use of case structure (“te, ni, wo, ha”), and so on. We will use NLP techniques to represent textual data as n-grams and word embeddings obtained from pre-trained models such as BERT (47).

Linguistic features considered to be characteristic of specific psychiatric diseases will be selected and statistically compared between groups (e.g., patients vs. healthy subjects, patients in different disease groups). This step is necessary to verify whether each variable has pathological validity before using it for machine learning.

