In the pilot study, we used 62-dimensional features for speech information and linguistic information. These features include linguistic features such as the number of morphemes, the number of vocabulary, the number of nouns, verbs, and adjectives, the number of particles “ga” etc., and the number of conjunction, and non-linguistic features such as the total time, the response time, the number of fillers, the formants. In the present study, we plan to use a total of about 100 independent variables for the analysis. We will also be employing dimension reduction and feature selection techniques to reduce the number of independent variables in the model. Based on the approximations, we estimate that the desired sample size is approximately 1,000. It should also be noted that the actual needed number of samples is likely to be lower.

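### Feature importance is assigned to a method such as XGBoost while several model types are evaluated, so the reported disease features may not be those of the model whose performance is reported

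*Protocol article*

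**What the plan says.** The abstract's aim includes "to quantify the linguistic features of those disorders using natural language processing", leading to biomarkers for diagnosis and severity.

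The Machine learning section gives the route. Disease features are to be extracted "relying on machine learning models such as decision trees, support vector machines (SVM), and deep learning architectures". Next, "Each model will be evaluated using cross-validation", and after that "the relative importance of each feature will be estimated using a feature importance estimation method such as XGBoost". The resulting features are carried forward: "We also plan to verify whether the features obtained in this manner can distinguish firstly between a normal and disease state", then between diseases, then for change in severity over time.

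Two other statements matter. Data processing and annotation plans group comparisons of candidate linguistic features before modelling: "This step is necessary to verify whether each variable has pathological validity before using it for machine learning". Sample size states that "we plan to use a total of about 100 independent variables for the analysis", with dimension reduction and feature selection to follow. The same section describes the pilot, in which XGBoost was the classifier.

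**The concern.** XGBoost is a learning algorithm, not a general-purpose way of measuring importance in other models. Its built-in importance scores say which variables its own trees split on and how much they helped. They say nothing about what an SVM or a neural network used. If the sentence is followed as written, accuracy could come from one model and the list of disease features from another.

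A second issue depends on detail that the article does not give. If the built-in score is gain on the training data, it is never negative, so an irrelevant variable that is split on at all gets some positive credit. Such a list has no zero point that separates useful features from useless ones.

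At stake is a main deliverable. The importance step produces the features that the study proposes to identify, quantify and then test against disease status and severity.

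**Working it through.** **1. Model mismatch (no arithmetic needed).** Set side by side:
- Models that are fitted and cross-validated: "decision trees, support vector machines (SVM), and deep learning architectures".
- Source of the importance ranking: XGBoost, as the only example given.
- Role of XGBoost elsewhere in the article: the predictive model of the pilot (Sample size).

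The text does not tie the ranking to the model whose performance is reported. The two coincide only if the reported model is the XGBoost fit itself, which the article does not say.

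**2. Scale of the problem, from the article.**
- The stated sample size reproduces: 10 cases per variable × 100 variables = 1,000.
- The Introduction targets 300–500 participants: 300/100 = 3 to 500/100 = 5 participants per variable.
- Each participant is followed two to five times (Clinical assessment), so records are not independent.

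**3. What training gain would do, if it were used.** This part is simulation. Its settings are assumptions, not document values: 100 independent normal features, boosted depth-3 trees, 60 trees, learning rate 0.1, and no prior screening.

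*Five true features at 0.5 SD, n=400.* Separate runs put 59%, 60% and 63% of total gain on the 95 irrelevant features. That share adds 95 small values and sets them against 5 large ones. Per feature, from the 59% run:
- irrelevant: 59% / 95 = 0.62%
- true: 41% / 5 = 8.2%
- ratio: 8.2 / 0.62 ≈ 13

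The ranking is accordingly good. On average 4.8 of the 5 true features were in the top 5 by gain in one run and 4.55 in another. Held-out permutation importance ranked no better (4.5 of 5). What differs is the zero point: about 77 of the 95 irrelevant features had positive training gain, whereas their held-out permutation importance averaged 0.00006, against 0.030 for true features.

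*Same signal, n=75.* This stands for 35 anxiety patients plus about 40 controls. The control count is inferred: the Discussion lists 102 + 89 + 58 + 35 + 79 = 363 patients among more than 400 participants, and 400 − 363 = 37. It is also an interim count. The irrelevant share of gain was 79%, and only 1.7 of 5 true features reached the top 5. Held-out permutation importance averaged −0.0002 for irrelevant and 0.023 for true features, but its rank order was also noisy.

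*Ten true features, varying strength (4 replicates each).*

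| n | Effect (SD) | Gain on irrelevant features | Irrelevant among top 10 |
|---|---|---|---|
| 400 | 0.5 | 43% | 12% |
| 400 | 0.3 | 64% | 43% |
| 1,000 | 0.5 | 25% | 0% |
| 1,000 | 0.3 | 51% | 12% |

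The n=1,000 rows treat cases as independent, which favours them, since the study's records are repeated on the same people. Comparing the last two columns shows that share of gain is a poor guide to ranking error.

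**4. Not tested.** All simulated features were independent. That trees split credit unstably among counts that rise together with speech length (morphemes, nouns, verbs, total time) is a reasonable expectation, not a simulated result.

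**The case against.** The sentence is open. XGBoost is only an example, trees are among the listed models, XGBoost is a tree ensemble, and the pilot used it as the classifier. If a boosted-tree model is the one reported, there is no mismatch. The article nowhere says that an SVM's accuracy will be paired with XGBoost importances. The type of importance and the data it is computed on are details that a condensed article may leave to a fuller plan. There are also safeguards: the group comparisons before modelling, dimension reduction, and the later check that selected features discriminate. The simulation includes none of these.

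Much of this stands. A reader might infer that the reported features would mostly be training noise, and might take the 59% and 79% shares as evidence. The document does not support that: it states neither training gain nor any other importance type, and at n=400 with 0.5 SD effects the ranking was nearly right despite those shares. The poor ranking at n=75 is mainly a limit of sample size, which a different importance measure does not remove.

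The objection does not remove the mismatch. The one example offered is a learner and not a method that applies across the listed models, so a fuller plan that follows this sentence would inherit the ambiguity. The safeguards are partial: none is said to sit inside the cross-validation or to use independent data, and none links the ranking to the reported model.

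**Conclusion.** The point holds as a fault of specification. The article evaluates several model types and names, for importance, a learner whose own scores describe only its own fit. The disease features reported may therefore not be those of the model whose performance is reported. This conclusion needs no simulation. It falls away only if the reported model is XGBoost.

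The noise issue is conditional on built-in training gain being used. Irrelevant features would then get positive credit without a null reference. The effect on the ranking is small at n=400 with 0.5 SD effects, and larger with weak signals (43% of the top 10 irrelevant at 0.3 SD with ten true features) or small groups. These sizes rest on assumed signal strength, independent features and no screening.

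No stated figure is wrong. The matter affects how a main deliverable is interpreted, and it is cheap to correct.

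**What to change.** Replace the importance sentence with one that says:

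- For each model whose performance is reported, permutation importance is computed on the held-out folds of the same cross-validation.
- Folds are split by participant, because each contributes two to five records.
- Features are permuted singly and, in addition, highly correlated counts are permuted as blocks (for example all part-of-speech counts together). Single permutation can understate a feature whose information is also carried by others; block permutation alone would give up the ranking of single features.
- The spread over repeated folds is reported as a measure of stability. It should not be presented as a calibrated confidence interval or used as a significance rule, because the folds overlap and about 100 features are examined.

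XGBoost can remain as one of the evaluated models, with its importance obtained in the same way.

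The cost is computing time and one paragraph of wording. Feature lists may become shorter, and in small diagnostic groups the ranking will remain noisy; the reported spread would make that visible.
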